## Abstract

**Aims:**

To evaluate the effectiveness of the ‘reserved therapeutic space’ intervention for improving the nurse–patient therapeutic relationship in acute mental health units in Spain.

**Design:**

Multicentre intervention study with control group.

**Methods:**

The study will be carried out in 12 mental health units. The ‘reserved therapeutic space’ intervention to be tested has been co‐designed and validated by both nurses and patients. The quality of the therapeutic relationship, the care received and perceived coercion among patients will be assessed. An estimated 131 patients per group are expected to participate. Funding was granted by the Instituto de Salud Carlos III. Co‐financed by the European Union (European Regional Development Fund (ERDF) (PI21/00605)) and College of Nurses of Barcelona (PR‐487/2021). The proposal was approved by all the Research Ethics Committees of participating centres.

**Results:**

This project will lead to changes in clinical practice, transforming the current models of organization and care management in mental health hospitalization units. No patient or public contribution.

## INTRODUCTION

1

The therapeutic relationship is internationally considered to be at the core of mental health nursing care (Moreno‐Poyato et al., 2016). Indeed, the quality of its establishment is associated with better evidence‐based practice on behalf of nurses (Moreno‐Poyato, Casanova‐Garrigos, et al., 2021). Moreover, the therapeutic relationship is used as a vehicle for improving the health of people with mental health problems (Zugai et al., 2015). However, the correct development and maintenance of the therapeutic relationship is complex and even more so in the context of inpatient mental health units (Molin et al., 2018; Moreno‐Poyato, El Abidi, Rodríguez‐Nogueira, et al., 2021). Therefore, it is necessary to design and evaluate interventions aimed at improving the therapeutic relationship in mental health units through the participation of all the main actors, both patients and professionals, and based on solid theoretical foundations and methodologically consistent designs (Hartley et al., 2020).

## BACKGROUND

2

In recent years, the national strategies on mental health in Catalonia and Spain have been aimed at person‐centred care and personal recovery. Thus, one of the main strategic lines of action is to improve care practices in relation to people's rights and to strengthen new capacities for the participation and empowerment of service users (Generalitat de Catalunya, Departament de Salut, 2017; Spanish Ministry of Health, 2022). In Spain, from a training point of view, one of the main challenges is to adapt the supply of training places for specialist nurses, as mental health nursing is recognized with an official postgraduate specialized training qualification (Spanish Ministry of Health, 2022). Along the same lines, the policy guidelines are committed to improving practice by promoting the active participation of professionals and users through the principles of dialogue, active listening and the person with mental health problems as a subject of rights (Generalitat de Catalunya, Departament de Salut, 2017; Spanish Ministry of Health, 2022). There is no doubt that it is through the therapeutic relationship that nurses in mental health care settings can enhance person‐centred practice (Tolosa‐Merlos et al., 2022). It is, therefore, a challenge for nurses to respond to these needs in the context of Spanish mental health inpatient units, where some users are admitted involuntarily (Wasserman et al., 2020) and remain in the hospital for an average stay of 15–16 days (Spanish Ministry of Health, 2022).

Multiple factors affect the quality of the nurse–patient therapeutic relationship in mental health units. First, factors related to the practice environment, such as the existence of biomedical models in the units (Roviralta‐Vilella et al., 2019), make it difficult to implement psychosocial interventions that improve the therapeutic relationship (Raphael et al., 2021). In this sense, other important environmental factors that have traditionally been identified as barriers to establishing quality relationships in the units are the lack of time on behalf of the nurses, either due to administrative tasks or due to a low nurse–patient ratio (Kingston & Greenwood, 2020). In addition, nurses consider the lack of leadership and support from supervisors to be an important limiting factor (Moreno‐Poyato, Rodríguez‐Nogueira, et al., 2021; Moreno‐Poyato, Roviralta‐Vilella, et al., 2021). Moreover, it should be considered that many units maintain outdated regulations and have structures that do not favour spaces for the relationship with the public (Adler, 2020; Tolosa‐Merlos et al., 2021). Most mental health units are locked units, which nurses perceive was causing their therapeutic relationship with the patient to get lost (Missouridou, Resoulai, et al., 2021). A good therapeutic relationship depends on the trust given to patients by keeping the doors open (Missouridou et al., 2022; Missouridou, Xiarhou, et al., 2021). Existing evidence also shows that nurses in acute mental health wards lack knowledge about how to engage effectively and in a way that helps their patients. Nurses affirm that this affects their education and training in the therapeutic relationship (McCluskey et al., 2022). Some studies have highlighted the importance of developing therapeutic relationship competence during training. Thus, there is a need to develop mental health professionals' therapeutic relationship knowledge and skills in professional training in acute mental health care (Liao & Murphy, 2019; Ruud & Friis, 2022). Consequently, all these factors contribute to patients reporting that nurses are often inaccessible and unavailable, indicating a lack of communication and a lack of opportunity to participate in their care (Rio et al., 2020). These aspects are basic for an effective nurse–patient therapeutic relationship (Aznar‐Huerta et al., 2021).

In recent years, different strategies have been implemented to improve the nurse–patient therapeutic relationship in mental health hospitalization units (McAllister et al., 2021; Molin et al., 2018; Moreno‐Poyato et al., 2018; Moreno‐Poyato, Rodríguez‐Nogueira, et al., 2021; Moreno‐Poyato, Roviralta‐Vilella, et al., 2021). Spaces for joint activities have been designed and implemented in the unit in a group setting to facilitate therapeutic engagement between nurses and patients (Molin et al., 2018). Combined strategies such as reflective staff groups and the use of individual daily interactions with patients have been used (Moreno‐Poyato et al., 2019). Group interventions in the form of clinical sessions for staff on patient case discussions have been carried out to improve understanding of the factors influencing patient behaviour (Berry et al., 2016). However, there is insufficient evidence that any intervention has demonstrated acceptable effectiveness (Hartley et al., 2020). Hence, the recommendations are aimed at constructing and evaluating interventions that involve the participation of both users and professionals, that are based on solid theoretical foundations and that propose methodologically consistent designs (Hartley et al., 2020).

Consequently, as a result of a participatory project with nurses from two mental health units, a nursing intervention was designed, implemented and evaluated, to enhance individualized encounters with their patients, obtaining excellent quantitative and qualitative results in the improvement of the therapeutic relationship (Moreno‐Poyato et al., 2018, 2019). Subsequently, 198 nurses from 18 mental health units participated in a new study in which they agreed on, implemented and evaluated a very similar intervention, which they called ‘reserved therapeutic space’ (RTS), emerging as part of one of the strategies to improve the therapeutic relationship of nurses with their patients (Moreno‐Poyato, Rodríguez‐Nogueira, et al., 2021; Moreno‐Poyato, Roviralta‐Vilella, et al., 2021). However, given the recommendations to design and validate the intervention with those people who will later form a relevant part of the intervention, a new study was carried out. This new study aimed at exploring the feasibility and validity of the intervention with participants with first‐person experience, belonging to two social activist organizations in the field of mental health, thus incorporating the patients' perspective of the intervention as protagonists (Moreno‐Poyato, El Abidi, Rodríguez‐Nogueira, et al., 2021).

## THE STUDY

3

### Aims

3.1

The main objective of this study is to evaluate the effectiveness of the RTS intervention in terms of its impact on the improvement of the nurse–patient therapeutic relationship in mental health inpatient units.

The secondary objectives of this study are to determine the effectiveness of the RTS in terms of its impact on:
The quality of the therapeutic relationship of nurses with their patients as perceived by people hospitalized in acute mental health units.The level of quality of psychiatric care perceived by people hospitalized in acute mental health units.The degree of coercion perceived by persons hospitalized in acute mental health units.

### Hypotheses

3.2

The RTS intervention improves the therapeutic relationship between nurses and patients hospitalized in mental health units.Hypothesis 1Inpatients receiving the RTS intervention by their referent nurse will have a higher difference in mean score relative to inpatients receiving standard care on the therapeutic relationship measure using the Working Alliance Inventory‐Short scale (WAI‐S).
Hypothesis 2Patients receiving the RTS intervention by their referring nurses will obtain a higher mean score difference compared to patients receiving standard care when measuring psychiatric quality of care using the Quality in Psychiatric Care (QPC) scale.
Hypothesis 3Patients receiving the RTS intervention by their referring nurses will obtain a lower mean score difference compared to patients receiving standard care on the measurement of perceived coercion using the Coercion Experience Scale (CES) instrument.

### Design

3.3

A multicentre intervention study with a control group aimed at evaluating the effectiveness of the RTS intervention under real clinical practice conditions versus usual care for patients in acute mental health units in Spain (Figure 1).

**FIGURE 1 nop21750-fig-0001:**
[figure not shown]
CONSORT Flow diagram RTS_MHNursing_Spain.

### Study setting and population

3.4

The study population will be patients hospitalized in acute mental health units in Spain. A total of 12 mental health hospitalization units will participate. The mental health units have been invited through the Spanish Association of Mental Health Nursing following territorial criteria of representativeness by autonomous community.

### Inclusion and exclusion criteria

3.5

Eligible subjects will be adults hospitalized in mental health inpatient units who voluntarily consent to participate in the study. Participants will be excluded if they present a language barrier, mechanical restraint, contraindication by the clinical referent, cognitive impairment or intellectual disability at the time of recruitment. To maximize the external validity of the study, no other exclusions will be made.

### Sample size

3.6

Accepting an alpha risk of 0.05 and a beta risk of 0.2 in a bilateral contrast, 131 subjects in the first group and 131 in the second group are required to detect a difference equal to or greater than 3 units. The common standard deviation is assumed to be 10 with a correlation coefficient between the initial and final measurement of 0.7. A loss‐to‐follow‐up rate of 20% was estimated.

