### Randomization

3.7

Given the difficulties due to the evaluation conditions in real clinical practice for a traditional randomization of the subjects or a randomization by clusters, and bearing in mind that not all the nurses in the units will participate in the intervention, the units will be paired by similarity of structural characteristics in terms of number of beds and will be randomized through a computer program to an intervention or control group. Randomization will take place prior to the training of the nurses and the recruitment of the subjects. The intervention will be blinded at the subject level.

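### The 131 per group assumes independently randomised patients, so the stated 80% power for 3 units does not hold for a design that randomises 12 hospital units.

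*Protocol article*

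**What the plan says.** The Sample size section (3.6) sets the error rates: "Accepting an alpha risk of 0.05 and a beta risk of 0.2 in a bilateral contrast". It then states that "131 subjects in the first group and 131 in the second group are required to detect a difference" of at least 3 units. On variability it says "The common standard deviation is assumed to be 10", with a "correlation coefficient between the initial and final measurement of 0.7", and it estimates a 20% loss to follow-up. No ICC, design effect, unit size or number of units appears in the calculation.

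The design sections describe a different structure. Study setting and population (3.4) says "A total of 12 mental health hospitalization units will participate". Randomization (3.7) pairs units on bed numbers, and these units "will be randomized through a computer program to an intervention or control group". Strengths and limitations (4.1) confirms that it is the centre that is randomised. Section 3.7 mentions difficulties with randomising by cluster, but what it goes on to describe is cluster randomisation.

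**The concern.** Every patient in a unit shares that unit's allocation, so the comparison between arms rests on 6 units against 6. If patients in the same unit resemble each other in how their scores change, they carry less information than the same number of independent patients, and a calculation that treats them as independent overstates power.

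The protocol's own Background (section 2) makes some resemblance likely. The influences on the therapeutic relationship that it lists operate at unit level: care model, nurse-patient ratio, leadership, ward rules and locked doors. Patients in intervention units also share a limited set of trained nurses (section 3.10).

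What is at stake is how the result is read. A beta of 0.2 tells readers that a non-significant result is fairly strong evidence against a 3-unit effect. If true power is well below 80%, that reading is wrong.

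**Working it through.** **Inputs from section 3.6:** two-sided alpha 0.05 (z = 1.96), power 0.80 (z = 0.8416), difference 3, SD 10, pre-post correlation 0.7, loss 20%. **From sections 3.4 and 3.7:** 12 units in pairs, so 6 per arm. **Assumed:** ICC of the change score 0.01 to 0.10 and equal unit sizes. The documents give neither.

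**Step 1. Reproduce 131.**
- Variance of change = 2 × 10² × (1 − 0.7) = 60.
- n per group = 2 × (1.96 + 0.8416)² × 60 / 3² = 104.65, so 105 evaluable.
- Allowing for loss: 104.65 / 0.8 = 130.8, so 131.

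Other routes do not give 131. A baseline-adjusted variance of 51 gives 112 with losses, follow-up scores alone give 219, and multiplying by 1.2 instead of dividing by 0.8 gives 126. The stated inputs thus account for the whole figure and leave no room for an unreported design effect. With independent patients, 105 per group gives 80.1% power, so there is no reserve either.

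**Step 2. Add the clustering.**
- Evaluable patients per unit: m = 105 / 6 = 17.5.
- Design effect: DE = 1 + (17.5 − 1) × ICC.
- Standard error: SE = √(2 × 60 × DE / 105).
- Power for 3 units: by normal approximation, and from the noncentral t distribution with noncentrality 3 / SE on 10 df (12 units less 2 arms) or 5 df (6 pairs less 1).

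| ICC | DE | SE | Power, normal | Power, 10 df | Power, 5 df | Detectable at 80%, 10 df |
|---|---|---|---|---|---|---|
| 0 | 1.000 | 1.069 | 80% | 72% | 62% | 3.3 |
| 0.01 | 1.165 | 1.154 | 74% | 65% | 55% | 3.6 |
| 0.02 | 1.330 | 1.233 | 68% | 59% | 50% | 3.8 |
| 0.05 | 1.825 | 1.444 | 55% | 47% | 39% | 4.5 |
| 0.10 | 2.650 | 1.740 | 41% | 35% | 29% | 5.4 |

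The 5 df column keeps the unpaired SE, so it assumes that matching on beds removes no between-unit variance.

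**Step 3. Could more patients in the same 12 units restore 80%?** By normal approximation with k = 6 units per arm, the evaluable number per group is 104.65 × (1 − ICC) × 6 / (6 − 104.65 × ICC). At ICC 0.02 this is 104.65 × 0.98 × 6 / 3.907 = 157.5, so 158, or 197 recruited after dividing by 0.8. The recruited numbers are 157 at ICC 0.01, 267 at 0.03 and 972 at 0.05. Above an ICC of 6 / 104.65 = 0.057, no number of patients is enough.

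**Step 4. Baseline adjustment.** Adjusting for the baseline score lowers the variance to 100 × (1 − 0.7²) = 51. Power on 10 df becomes 72%, 66%, 53% and 39% at ICC 0.01, 0.02, 0.05 and 0.10.

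**The case against.** The strongest reply concerns the size of the shortfall.

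- **Degrees of freedom.** The 10 df figures combine two penalties, the design effect and a small-sample test on 12 units. At ICC 0 a patient-level test does have about 80% power; the 72% arises only if inference is made at unit level. This is fair, and it is why the table shows the columns separately. But patient-level inference is no way out once the ICC is positive. Ignoring clustering at ICC 0.01 to 0.05 would raise the nominal 5% error to about 7% to 15%, from 2 × (1 − Φ(1.96 / √DE)).
- **Pairing.** The 5 df figures are a worst case. If bed-matching removed half of the between-unit variance, they would be 58%, 56%, 49% and 40% instead of 55%, 50%, 39% and 29%. This stands, and the figures still fall well short of 80%.
- **ICC.** No value is in the documents, and the relevant ICC is that of the change score. Stable differences between units cancel in a change score, so this ICC may differ from that of the raw scores. This stands: the size is conditional on it.
- **Losses.** If all 131 per group were evaluable, power at ICC 0.01 would be 81% by normal approximation and 73% on 10 df; at 0.02 it would be 75% and 66%. But the plan itself expects 20% loss.
- **Baseline adjustment.** By normal approximation it reaches 80.5% at ICC 0.01 but only 75% at 0.02. The Data analysis section (3.11) enters pre-post differences, and section 3.6 claims no such gain.

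None of these points supplies the missing clustering allowance.

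**Conclusion.** The concern holds. The arithmetic behind 131 is correct, but for a trial that randomises patients one by one. With the planned 20% loss and the change-score method that the figure rests on, 80% power is reached only if the ICC is essentially zero and inference is made at patient level. The direction does not depend on the assumed ICC, because the calculation has no slack.

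The size does depend on it. For a change-score ICC of 0.01 to 0.10 and equal unit sizes, power for 3 units is 65% to 35% on 10 df, or 74% to 41% if only the design effect is counted. On 10 df the difference detectable with 80% power is 3.6 to 5.4 units, not 3. At ICC 0.02 the trial would miss a true 3-unit effect about 40% of the time (1 − 0.59 = 0.41), twice the stated beta. Unequal unit sizes would lower power further.

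**What to change.** Rewrite section 3.6, keeping 12 units and 131 per group:

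- Call the design cluster-randomised, here and in section 3.7, with the unit as the randomised entity.
- State the assumed ICC of the change score, its source and a plausible range.
- Give the number of units per arm, the expected evaluable patients per unit (17.5 after losses) and the design effect 1 + (m − 1) × ICC.
- Report the resulting power for 3 units, or the difference detectable with 80% power, and the degrees of freedom used (10, or 5 if the pairs are kept). If ICC 0.02 were adopted, for example, this would read as about 59% power for 3 units, or 80% power for 3.8 units, on 10 df.
- If the 5 df figures are shown, say that they assume matching on beds removes no between-unit variance.
- Name the WAI-S as the scale on which the 3 units are measured.
- Delete the claim that 131 per group gives 80% power for 3 units.

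This does not raise the power; it makes the stated power true. A baseline-adjusted analysis that respects the units would recover part of the loss (66% at ICC 0.02 on 10 df). The cost is one paragraph with a less favourable figure, and no extra patients or units.

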### Randomization

3.7

Given the difficulties due to the evaluation conditions in real clinical practice for a traditional randomization of the subjects or a randomization by clusters, and bearing in mind that not all the nurses in the units will participate in the intervention, the units will be paired by similarity of structural characteristics in terms of number of beds and will be randomized through a computer program to an intervention or control group. Randomization will take place prior to the training of the nurses and the recruitment of the subjects. The intervention will be blinded at the subject level.

### The intervention

3.8

The RTS (Moreno‐Poyato, El Abidi, Lluch‐Canut, et al., 2021) is an intervention that will be carried out by nurses from mental health hospitalization units together with the hospitalized persons for whom they are referents. To ensure the fidelity of the intervention, the nurses of the centres selected for the intervention, and who agree to collaborate in the study, will receive complementary training from the research team prior to initiating recruitment, in addition to a brief guide to the implementation of the intervention. Likewise, the intervention will be interrupted if the assigned nurse were to take sick leave or transfer to another service and/or if the patient were to resign to continue the study. Furthermore, to improve compliance with the intervention protocol, in addition to other recommendations, the guidelines include recommendations for nurses to record the sessions in the patient's clinical history.

The main objective of the RTS intervention is to enhance the therapeutic bond of trust, to enable the agreement of objectives and interventions in a shared manner in relation to their recovery process in the unit. The intervention is carried out through individual meetings between the nurse and the patient in a comfortable and intimate space, where there are no interruptions and which is also chosen by the person who is hospitalized. The content of the spaces must be constructed individually according to the patients' concerns at each moment of the process.

The intervention consists of three phases:
Phase one or orientation meeting: this should take place within the first 24–72 h of hospitalization at the request of the referring nurse for the patient's stay. It is aimed at making contact and building a bond of trust. In this first meeting, the patient's main concerns should be identified and, as far as possible, an agreement should be established for the following follow‐up meetings. Possible topics to be discussed at this stage are the unit's regulations (permissions, visits, objects, etc.), the vulnerability of rights, the experience of involuntary admission or even feelings of guilt in relation to what is happening to the patient.Phase two, with follow‐up meetings: during the following days of the hospitalization, these meetings should take place at the patient's request and the number of meetings should be as many as the patient requests and the nurse is able to offer. To facilitate this, the nurse should demonstrate availability, so that each day at the beginning of the shift, the nurse should greet and invite the patient to meet up during the working day. Similarly, at the end of the shift, the nurse should say goodbye and invite the patient for the next working day. As for the content of the meetings during this phase, the topics to be discussed will once again be determined by the patient's concerns at the time regarding his or her hospitalization process. To facilitate the development of the meetings in this phase, the key topics are the side effects of the medication, the duration of the admission, the extra medication or the incidents in the unit.Phase three, with a farewell meeting: in the pre‐discharge stage of hospitalization, in this last meeting it is important for the nurse to positively reinforce the patient's evolution in the hospitalization process in order to empower the person, but also to help to provide guidance at the time of discharge from the unit. In this meeting, it is especially important to provide information on resources and continuity of care outside the acute care unit. Likewise, to resolve doubts and concerns about future plans and to recommend strategies for the prevention of relapses.

